## 6.7 Statistical methods

### 6.7.1 Analysis of clinical study outcomes

Study data that has been captured into a secured database (see “7.1.1 Data collection”) will be exported and loaded into a statistical software programme for statistical analysis without any presence of any personal identifying information.

### 6.7.2 Analysis of clinical study outcomes

In univariate analysis on dichotomous variables the  $\chi^2$ -test will be used. Continuous variables will be analysed using the Student t-test or Mann-Whitney U test. For dichotomous primary outcome measures the relative risk, absolute risk and risk difference will be reported. Continuous variables will be summarized by medians with interquartile range and means with standard deviations. For univariate analysis on continuous outcomes mean differences will be reported. For survival analysis the Cox proportional hazards model will be used, and hazard ratio's will be reported. Assessment of risk factors for therapy failure as well as its potential interaction with patient health and QoL will be performed using multivariate analysis. All results will be reported along with 95% confidence intervals.

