## 4 STUDY DESIGN AND PATIENT POPULATION

### 4.1 Study format\*

The study format will be an open-label randomized controlled trial (RCT) in which HIV-1 infected patients initiating ART and already on ART will be enrolled. Enrolment will continue until 600 patients have been randomized. Patients initiating ART will be randomized after six months of ART and patients already on ART will be randomised at 6 months after the last viral load measurement. Patients in both arms will receive study visits every three months for a total follow-up duration of 18 months after randomisation to either of two study arms.

- Control arm: Standard of care HIV-1 treatment monitoring in accordance with South African NDOH guidelines. (see “5.1.2”)
- Intervention arm: Intensified treatment monitoring according to the treatment monitoring strategy under investigation. (see “5.1.3”)

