#### 5.2.7 Questionnaires

Questionnaires will be used to measure a variety of parameters relevant to the trial study objectives (see table 2). For data on adherence (e.g. number and reasons of missed doses, reasons and motives for non-adherence), drug toxicity and physical and mental wellbeing, a questionnaire developed by the AIDS Clinical Trial Group (ACTG) will be used. This validated self-report questionnaire has been included in several clinical trials and consists of a baseline and follow-up questionnaire. A modification of the ACTG baseline questionnaire will be used at enrolment, and a shortened version of the ACTG follow-up questionnaires will be used at month 3, 6, 9, 12, 15, 18, 21 and 24 (study end) in both study arms. Data on adherence from the standard pill count form that is applied at each drug pick-up visit (monthly or every 2 months) will also be collected.

Data relevant to the study objectives regarding social and psychological risk factors are partly covered by the ACTG questionnaires. A newly designed questionnaire will be used that will incorporate the sections from the ACTG questionnaires (mental and physical health), NIDS (socioeconomic status and family structure), CHAMP (substance abuse and sexual risk behavior). This questionnaire will contain item scales modified from the ACTG original, matched to local socio-economic and cultural context, as well as record several additional parameters such as stigmatization (Kalichman & Simbayi) and coping abilities (CISS). Data on Quality of life (QoL) of study participants will be used for evaluation of the cost-effectiveness of the trial intervention and will be recorded using the WHO QOL HIV (BREF) questionnaire and EQ5D questionnaire.

In a substudy participants who become lost to follow-up during the trial and who are successfully traced >28 days after a missed clinical visit (as per standard-of-care clinical procedures) are approached for informed consent to perform an additional questionnaire interview during a home visit.

Questions will be bundled in a comprehensive baseline and study end questionnaire (baseline and month 24), and a brief follow-up questionnaire which will be recorded per 3-monthly study visit (month 3, 6, 9, 12, 15, 18 and 21). In lost to follow-up patients who enter the substudy questionnaires will be recorded during a home visit. For a full overview of parameters and questionnaires, see table 2.

Table 2: overview of questionnaire data

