| Parameters                                                                                                                         | Time of collection                                    | Source                                                                                             |
|------------------------------------------------------------------------------------------------------------------------------------|-------------------------------------------------------|----------------------------------------------------------------------------------------------------|
| Socio-economic status
- Demographics (1)
- Employment (2)
- Household composition (3)
- Food insecurity (4)            | Baseline                                              | - NIDS wave 3 Adult questionnaire
- NIDS wave 3
- NIDS wave 3
- SAHANES                   |
| Health
- Mental health (5)
- Physical health (6)                                                                             | Baseline & study end                                  | - PHQ-9                                                                                            |
| Transmission factors
- Sexual risk behaviour (7)
- Transactional sex (8)                                                     | Baseline                                              | - CHAMP
- CHAMP                                                                                 |
| Adherence factors
- Attitudes toward therapy (10)
- Stigmatization (11)
- Coping abilities (12)
- Substance abuse (13) | Baseline
Baseline
Baseline
Baseline          | - ACTG Baseline & FU
- Kalichman&Simbayi
- CISS-21
- CHAMP                                |
| Pill counts and self-reported adherence (SoC)                                                                                      | Baseline & every 3 months home visit in LTFU patients | South African NDoH standard of care pill count form                                                |
| Quality of life
- HIV-related QoL
- QoL for QALY valuation                                                                   | Baseline & every 3 months                             | - WHO QOL HIV (BREF)
- EQ5D                                                                     |

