## 6 OUTCOMES AND ANALYSIS OF RESULTS

### 6.1 Virological and clinical effects of intensified monitoring

Virological outcomes will be differences between arms in (1) the number of drug resistance mutations present, (2) the selection of specific resistance mutations associated with multi-drug resistance (presence of the K65R mutation, or the presence of >1 NNRTI mutation) and (3) consequential loss of therapeutic options. Furthermore, (4) the rate of virological failure in the absence of drug resistance in both arms, unnecessary treatment switches averted in the intervention arm and unnecessary therapy switches made in the control arm will be assessed. An averted case of unnecessary switching will be defined as two sequential elevated VL results in the intervention arm without presence of resistance mutations. Assessment of unnecessary switching in the control arm can be ascertained by retrospective genotypic resistance testing.

Additional virological outcomes will be (5) the time on a failing regimen, defined as the time during which viremia > 1000 copies/mL is maintained after the first instance of a viral load >1000 copies/ml (6) The loss of second line therapeutic options over time in the presence of a failing regimen. Comparison of the extent of drug resistance between both groups will allow for assessment of the clinical consequences of resistance development in both arms. (7) The influence of genotypic resistance testing on the choice for a second line regimen. Genotypic resistance testing results enable the physician to make an informed decision with regard to a follow-up regimen to the first-line regimen. By comparing the chosen regimens in the intervention and control groups, the effect of the availability of genotypic resistance data on clinical decision-making will be compared. These outcomes can be compared between both arms as VL and CD4 measurements will be performed retrospectively in the control group, resulting in an equal frequency of measurements between both arms.

Clinical outcomes will be decrease in CD4 count during failure, QoL as measured using a validated QoL questionnaire, and recorded events of patient morbidity and mortality that can be related to immunological failure.

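### Section 6.7.2 compares quality of life between arms with unadjusted two-sample tests and leaves the score collected before randomisation unused: a valid analysis, but less precise than it could be

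*Protocol*

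**What the plan says.** Protocol 3.2.1 lists quality of life first among the clinical effects, which are secondary objectives. Section 6.1 names the outcome as "QoL as measured using a validated QoL questionnaire" and gives neither a time point nor a summary measure.

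On timing, Table 2 in 5.2.7 schedules both quality-of-life instruments at "Baseline & every 3 months", and Table 3 shows the same visits for both arms. Section 4.1 states that "Patients initiating ART will be randomized after six months of ART"; patients already on ART are randomised six months after their last viral load. Every patient therefore has at least one score before randomisation. A newly initiated patient has up to three (baseline, month 3, month 6). Six further scores are scheduled afterwards, at months 9, 12, 15, 18, 21 and 24.

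On analysis, 6.7.2 says "Continuous variables will be analysed using the Student t-test or Mann-Whitney U test" and "For univariate analysis on continuous outcomes mean differences will be reported". It adds: "All results will be reported along with 95% confidence intervals". The one sentence there that links quality of life to a multivariable method concerns something else: "Assessment of risk factors for therapy failure as well as its potential interaction with patient health and QoL will be performed using multivariate analysis". Section 6.5 likewise uses multivariable regression for risk factors and not for the comparison of arms.

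**The concern.** The trial pays for a quality-of-life score before randomisation in every patient, and 6.7.2 then names comparison methods that do not use it. Scores on such instruments usually differ a good deal between patients and persist within a patient. Part of the spread in a follow-up score can therefore be predicted from the earlier score and removed from the comparison. A two-sample test on the follow-up score leaves that spread in the standard error.

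What is at stake is the width of the confidence interval for a secondary outcome. Section 3.2.1 already doubts whether follow-up is long enough for clinical differences to appear, so precision given up here is precision the trial can use. Section 5.2.7 also says the quality-of-life data will serve the cost-effectiveness evaluation, so any direct comparison of EQ5D between arms would carry the same loss.

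**Working it through.** The protocol gives no sample size, power, standard deviation or target difference for quality of life, so there is no figure to reproduce. The check compares the precision of the named test with that of an adjusted analysis of the same visit.

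**Inputs from the protocol**
- 300 patients per arm (5.1.2, 5.1.3).
- Loss to follow-up of 10% a year (6.7.3) over 18 months after randomisation (4.1): 300 × (1 − 0.15) = 255 evaluable per arm. Compounding gives 300 × 0.9^1.5 = 256, which makes no practical difference.
- 95% confidence intervals (6.7.2), hence a two-sided 5% level.

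**Assumptions not in the protocol**
- Correlation ρ between the pre-randomisation and follow-up scores of 0.3, 0.5 or 0.7.
- Equal variance at the two time points.
- A true difference of 0.2 SD at the visit analysed.

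**Formulas.** In SD² units, the variance factor for one visit is v = 1 without adjustment and v = 1 − ρ² with linear adjustment for the earlier score. The standard error of the arm difference is √(2v/255). Power is approximately Φ(0.2/SE − 1.96).

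| Analysis of one visit | v | Variance of unadjusted ÷ this | SE (SD units) | 0.2/SE | Power |
|---|---|---|---|---|---|
| Two-sample t-test | 1 | 1 | 0.0886 | 2.26 | 62% |
| Adjusted, ρ = 0.3 | 1 − 0.09 = 0.91 | 1.10 | 0.0845 | 2.37 | 66% |
| Adjusted, ρ = 0.5 | 1 − 0.25 = 0.75 | 1.33 | 0.0767 | 2.61 | 74% |
| Adjusted, ρ = 0.7 | 1 − 0.49 = 0.51 | 1.96 | 0.0632 | 3.16 | 88% |

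The powers shown use the t distribution; the normal formula agrees to within 0.2 percentage points. The confidence interval narrows by the factor √v: 0.95, 0.87 or 0.71 of its unadjusted width.

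**Validity of the named test.** In 5,000 simulated trials per value of ρ with no true difference and 256 per arm, the two-sample t-test rejected in 5.4%, 5.1% and 5.0% of trials on the final-visit score. On change from baseline it rejected in 4.6%, 4.6% and 5.1%. The 5% level is kept when each patient contributes one value.

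**The case against.** The strongest reply is that the named test is not wrong. The arms contain different patients, so an independent two-sample test is the right family for the contrast, and it holds its error rate. Randomisation makes the unadjusted difference unbiased, and its confidence interval already allows for chance imbalance. The choice of summary measure, visit and covariance structure for a repeated secondary outcome commonly belongs in a statistical analysis plan, which is not shown here. All of this stands. The missing time point is therefore not raised as a fault. What 6.7.2 does state is the test, and a plan that adjusted for the earlier score would depart from it.

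Three stronger readings are tempting, and the protocol supports none of them.

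- A reader might infer that the tests mishandle the repeated measurements and inflate the false-positive rate. That happens if all six visits are pooled as independent records (about 29% at ρ = 0.5) or if any one of six separate visit tests counts as positive (about 20%). The protocol plans neither.
- A reader might set the 62% power of a single visit against about 97% for an adjusted average of six visits. That figure assumes the full 0.2 SD effect is present from month 9. Under 5.1.3, month 9 is the first viral load of the intensified schedule, and drug-level testing and tailored counselling come four weeks later, only after an elevated result. If the effect instead rose linearly from 0 at month 9 to 0.2 SD at month 24, the average would be 0.1 SD. The adjusted average would then have about 50%, 50% and 60% power at ρ = 0.3, 0.5 and 0.7. The contrast also passes over the named t-test applied to each patient's six-visit mean, which is valid and reaches 84% at ρ = 0.5 under the same constant effect.
- A reader might conclude that the cost-effectiveness result is distorted. Section 6.3 describes a Markov model that draws on South African evidence, and nothing says that trial utilities enter it through the 6.7.2 test.

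**Conclusion.** The point holds as a minor loss of precision on a secondary outcome. The protocol collects a quality-of-life score before randomisation in every patient, and 6.7.2 does not use it in the between-arm comparison. At any one follow-up visit the unadjusted analysis has 1.10, 1.33 or 1.96 times the variance of the adjusted one if the correlation is 0.3, 0.5 or 0.7. For a 0.2 SD difference with 255 per arm, that is 62% power against 66%, 74% or 88%.

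The correlation and the 0.2 SD are assumptions. The variance ratio depends only on the correlation (with equal variances); the powers depend on both. At the low end of the range the gain is small. No primary conclusion is affected.

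**What to change.** In 6.7.2, add a paragraph for quality of life. Analyse it with a linear model at one chosen visit, or with a mixed model for repeated measures on the scores from months 9 to 24. Either way, adjust for the last score recorded before randomisation. Choose one contrast in advance, for example the arm difference at month 24, and report it with its 95% confidence interval. Treat any trial-based comparison of EQ5D between arms in the same way. The t-test and Mann-Whitney U test can stay for continuous outcomes that have no pre-randomisation value.

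The cost is one paragraph and slightly more analysis work. Every score needed is already scheduled in Tables 2 and 3, so no visits, measurements or patients are added.

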### 6.7.3 Sample size calculation

Sample size calculation is based on power analyses using selection of resistance as the primary study outcome. The first outcome used for power calculation is the selection of non-polymorphic K65R drug resistance related mutation in HIV reverse transcriptase that is selected by currently used first line therapy at any time during study follow-up. Previously observed prevalence rates of the K65R mutation in HIV-1 subtype C infected patients experiencing therapy failure of a first-line regimen are 70% in LMIC and 17% in developed settings. Using a  $1-\alpha$  of 0.9 and a  $\beta$  of 0.05, the inclusion of 14 cases of failure per arm is needed. Cumulative virological failure (VL >1000 copies/ml) is anticipated to occur in 15% of patients at 12 months after initiation of ART and at 20% at 18 months. Taking into account a loss to follow-up of 10% per year and 20% failure rate, 83 patients are needed per study arm

to detect differences in resistance development as described in literature.

The study is also powered to detect the expected differences in selection of multiple resistance mutations in both arms at month 18 after therapy initiation, derived from a pilot study we performed at Ndlovu Medical Centre. In this study we saw an increase of 2.8 to 4.3 mutations per additional 6-12 months of prolonged therapy. This difference can be detected with 10 patients with therapy failure (59 patients per study arm at an expected failure rate of 20% and 10% loss to follow-up a year).

The third outcome used for power calculation is based on a cross-sectional analysis of a detectable VL >1000 copies/ml at the end of the trial (study month 24). The number of patients with a VL test result above 1000 copies/mL is estimated to be 15% in the control arm and 5% in the intervention arm. Taking into account a loss to follow-up of 10% a year, initial inclusion of 216 patients per arm is required to detect the anticipated difference.

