## 5 DESIGN & METHODS

### 5.1 Study design

#### 5.1.1 Inclusion, observational follow-up & randomisation (baseline to month 6 of ART)

Eligible patients attending Ndlovu Medical Centre will be recruited as described under “6.2.2 Recruitment procedure” and “6.2.5 Informed consent”. A subgroup of patients is enrolled prior to start of ART in order to collect baseline plasma samples and data on potential risk factors for therapy failure. These patients will receive observational study follow-up visits at month 3 and month 6 after start of ART. In standard of care, at month 6 of ART a VL measurement is performed to determine initial treatment success, indicated by suppression of the VL to <1000 copies HIV-1 RNA/ml. To ensure that only patients with initial treatment success are selected for randomisation, randomisation will be performed after availability of the month 6 VL into either the control arm or intervention arm. (described under “7.2.4 Randomisation procedure”). In addition, a group of patients already on ART and with a last annual VL result of <1000 copies/ml obtained <6 months previously will be enrolled, and will be followed observationally until 6 months after the last viral load, at which point these patients will be randomised in the same fashion. After randomisation, patients in both study arms will return for study follow-up visits on a three-monthly basis, at month 9, 12, 15, 18, 21 and 24 after start of ART or after the last VL measurement. In addition, patients will be called back for additional study visits (max. 2) in case of a detected VL >1000 copies/ml during any of these visits. All visits in both arms, including aforementioned additional call back visits will coincide with standard of care medication collection visits to the clinic. In case of a switch to second-line therapy, patients in both arms will continue three-monthly follow-up visits in an observational manner, and guidelines for monitoring of second-line therapy are followed.

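### Section 6.7.3 swaps its error-rate labels, sets 14 failures per arm where the planned chi-square test needs 17 for 90% power, and uses a failure rate that does not describe the randomised patients

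*Protocol*

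**What the plan says.** Protocol section 6.7.3 gives three sample-size calculations.

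- **K65R among failures.** The assumed prevalences "are 70% in LMIC and 17% in developed settings". With 1−α written as 0.9 and β as 0.05, the section states "of 0.05, the inclusion of 14 cases of failure per arm is needed" (the 0.05 is the value given for β). Cumulative virological failure "is anticipated to occur in 15% of patients at 12 months after initiation of ART and at 20% at 18 months", and the enrolment follows: "Taking into account a loss to follow-up of 10% per year and 20% failure rate, 83 patients are needed per study arm".
- **Number of mutations.** The difference is 2.8 v 4.3 mutations. "This difference can be detected with 10 patients with therapy failure", converted to 59 per arm at the same 20% failure and 10% yearly loss.
- **VL above 1000 copies/ml at month 24.** 15% v 5% requires 216 per arm after allowing for loss.

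Sidedness is not stated. Section 6.7.2 names the chi-square test for dichotomous variables and adds: "All results will be reported along with 95% confidence intervals". Section 5.1.1 places randomisation after the month-6 VL: "To ensure that only patients with initial treatment success are selected for randomisation". Section 4.5 also admits ART-naive patients who are viraemic at month 6 but resuppress by month 9. Section 4.2 adds patients with at least 1 year of suppressive ART. Section 4.1 sets 18 months of follow-up after randomisation and 600 randomised patients, 300 per arm.

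**The concern.** Section 6.7.3 calls selection of resistance the primary study outcome, and this paragraph is its numerical justification. Three things in it do not hold together.

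1. Read as written, the test level is 10% and the power 95%. That conflicts with the 95% intervals in section 6.7.2 and with the section's own 216.
2. The 14 failures do not deliver the intended power with the test that section 6.7.2 names.
3. The 20% used to turn failures into patients runs from ART initiation to month 18. The patients to whom it is applied enter only after month 6, only if suppressed, and some have been suppressed on ART for a year or more.

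At stake is whether the stated error rates, failure count and per-arm figures can be relied on.

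**Working it through.** **Inputs, all from section 6.7.3:** K65R 70% v 17%; VL above 1000 at month 24, 15% v 5%; failure 20%; loss 10% per year. Over the 18 months after randomisation (section 4.1) loss is 10% × 1.5 = 15%, so 85% are retained.

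**Step 1. Reproduce the plan's figures.** The unpooled normal formula is n = (z₁₋α/₂ + z₁₋β)² × [p₁(1−p₁) + p₂(1−p₂)] / (p₁−p₂)².

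| Reading | (sum of z)² | 70% v 17% | 15% v 5% | 15% v 5% ÷ 0.85 |
|---|---|---|---|---|
| α 0.05 two-sided, power 0.90 | 10.507 | 10.507 × 0.3511 / 0.2809 = 13.13 → 14 | 10.507 × 0.175 / 0.01 = 183.9 | 216.3 |
| As written: α 0.10, power 0.95 | 10.822 | 13.53 → 14 | 189.4 | 222.8 |

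Enrolment: 14 / 0.20 / 0.85 = 82.4 → 83, and 10 / 0.20 / 0.85 = 58.8 → 59. So 14, 83, 59 and 216 all follow from a two-sided α of 0.05, power 0.90 and unpooled variance. The literal reading also gives 14 and 83 but misses 216. The labels are swapped, and the swap has no effect on 14 or 83.

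**Step 2. Power of 14 failures with the planned test.** Enumerating both binomial distributions (70% v 17%, equal arms) for the uncorrected chi-square test at two-sided 0.05:

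| Failures per arm | Exact power |
|---|---|
| 14 | 83.3% |
| 16 | 89.9% |
| 17 | 92.1% |

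At the literal α of 0.10, 14 failures give 91.1% against a literal target of 95%. The target is missed under either reading. The pooled-variance formula agrees: it gives 16.2 → 17. Enrolment for 17 at the plan's own rates is 17 / 0.20 / 0.85 = 100 per arm, not 83.

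**Step 3. The clock and the population behind 20%.** In 14 / 0.20 / 0.85 the 0.85 runs for 18 months from randomisation, while the 0.20 runs for 18 months from ART initiation. Part of the 20% falls before randomisation, and those who do not resuppress by month 9 never enter. Against that, follow-up runs to month 24, six months beyond the 20% figure. For the on-ART cohort a rate from initiation has no direct meaning.

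The document gives no month-6 or month-24 cumulative rate. As an illustration only, assume 5–10% by month 6 and 20–25% by month 24, and remove all month-6 failures:

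- lowest: (0.20 − 0.10) / 0.90 = 11.1%, so 14 / 0.111 / 0.85 ≈ 148 per arm;
- highest: (0.25 − 0.05) / 0.95 = 21.1%, so 14 / 0.211 / 0.85 ≈ 78 per arm.

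This range contains the plan's 20% and 83.

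**Step 4. What 300 per arm gives.** Retained: 300 × 0.85 = 255.

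- 15% v 5%: exact chi-square power about 97%.
- K65R, with the number of failures set at its expected value: 51 failures at 20% (above 99.9%), 28 at 11% (98.9%), 17 at 17/255 = 6.7% (92%).

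**The case against.** **The swap is harmless.** It is true that 14 and 83 survive it, and the 95% intervals make a 10% test level an unlikely intention. A reader might infer that the transposition invalidates the per-arm figures. It does not. What stands is that the protocol misstates its own significance level and power.

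**Fourteen is a choice of approximation.** A comparison based on the unpooled (Wald) risk difference has exact power of 90.4% at 14 per arm, and a pooled formula at one-sided 0.05 also gives 14. But section 6.7.2 names the chi-square test, and one-sided 0.05 with power 0.90 would give 176 (unpooled) or 180 (pooled) per arm for the third outcome, not 216. The objection shows where 14 came from; it does not show that the named test has 90% power.

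**A shortfall in failures is not shown.** This stands. A reader might infer that failures will be fewer than planned. Selecting suppressed patients pushes the rate down, but follow-up to month 24 and the admission of patients who resuppress by month 9 push the other way, and the illustrative range includes 20%.

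**Month 18 in the control arm.** The mutation-count comparison is set at month 18, when that arm has no scheduled VL, and a reader might infer that it cannot be made. Sections 5.1.2, 5.2.2, 5.2.6 and 6.1 answer this: plasma and DBS are stored at that visit, and retrospective VL and resistance testing is planned for control-arm failures.

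**The 10 failures lack an SD.** This is a reporting gap only. For a difference of 1.5 mutations with 10 per arm, a t-test at two-sided 0.05 has about 89% power if the SD is 1.0 and 56% if it is 1.5. The claim can be neither confirmed nor refuted.

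**Conclusion.** The point holds as a defect of reporting and assumption, in three parts.

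- **Labels.** The error rates are transposed. The intended values are a two-sided α of 0.05 and power of 0.90. There is no numerical effect on 14 or 83.
- **Failure count.** Fourteen failures per arm give about 83% exact power with the planned chi-square test, against an intended 90%. Seventeen are needed, or 100 per arm at the protocol's own 20% and 15%. This rests on no outside assumption.
- **Failure rate.** The 20% belongs to a different start time and a different population, so 83 and 59 are not justified for the patients randomised. The direction and size of any error cannot be established from the document.

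A reader might conclude that the trial is underpowered for K65R. The document does not support that. Neither 83 nor 59 is the operative size, and at 300 per arm K65R power is about 99% even at 11% failure and stays above 90% down to about 7%. Those figures assume 15% loss, 70% v 17%, and failures at their expected number.

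**What to change.** In section 6.7.3:

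1. Write two-sided α = 0.05 and power = 0.90, and name the formula or test used.
2. Replace 14 failures per arm by 17 (chi-square), or keep 14 and state that it gives about 83% power.
3. Replace the 20% by an assumed failure probability from randomisation to month 24, given separately for the ART-naive and on-ART cohorts with its basis, and restate 83 and 59 from it.
4. State the power that the planned 300 per arm gives: about 97% for 15% v 5% at month 24, and above 90% for K65R if about 7% or more fail.
5. Optionally, give the SD, α and power behind the 10 failures in the mutation-count calculation.

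The cost is restated text and figures. No change to enrolment, visits or procedures follows.
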